### Interim analyses {21b}

When 50% of patients have been randomized and completed 6 months of follow-up, the primary endpoint will undergo an interim analysis by a statistician and the results will be presented to the trial data monitoring committee (DMC). Based on the assessment by the DMC, the trial may be stopped or undergo appropriate modifications. Furthermore, the decision to terminate the trial will be made solely by the trial data monitoring committee (DMC) or the trial management team in the event of a serious adverse event, serious safety issue, inability to continue the trial, or failure to demonstrate a predetermined hypothesis.

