### Trial design {8}

To evaluate the efficacy of combining DBM with ADIM in patients with stroke, a randomized controlled trial utilizing a parallel design and employing an assessor-blinded methodology will be conducted. Participants are all inpatients of the Neurorehabilitation Department of Shanghai Second Rehabilitation Hospital who correspond with the inclusion criteria. The research projects are registered with the Chinese Clinical Trials Registry (ChiCTR-2100054897), and the study has been approved by the Ethics Committee of the Shanghai Second Rehabilitation Hospital (Shanghai, China). All participants will be informed of the trial and will sign a written informed consent form.

Patients who meet the inclusion criteria will be randomly grouped after basic data collection. This will be done by using a computer-generated random number table to randomly divide the subjects into a control group (receiving 4 weeks of conventional rehabilitation without other specific exercise interventions), and a study group (receiving 4 weeks of DBM + ADIM intervention alongside conventional rehabilitation) in a 1:1 ratio. Random numbers will be placed in opaque envelopes by independent persons not involved in this experiment to achieve allocation concealment. As this study uses an exercise intervention, it will be difficult to conceal the grouping from the therapist and subjects, but it will be possible to blind the outcome indicator measurer. We will arrange for a new assessor to replace the assessor familiar with allocation to achieve single blinding.

In this trial, a superiority trial framework has been established to examine a specific core training approach, with the aim of improving walking function in patients with stroke. The trial process includes an initial assessment one week before the start date, a final assessment post-trial, and a follow-up evaluation six months later. These evaluations serve the purpose of measuring treatment effectiveness, assessing potential side effects, and documenting relevant baseline data and clinical information of the participants. The study procedure is shown in Fig. 1 and the period of the study in Fig. 2. The program follows the principles of SPIRIT 2013.

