### Intervention description {11a}

Control group (CG)Patients in the control group will receive routine rehabilitation training. Routine rehabilitation training will include (1) motor therapy and functional training for hemiplegic limbs; (2) sitting and standing balance training; (3) weight transfer training; (4) walking training; (5) and ADL training, among others. The therapist will inform the patient of the training prior to carrying out the rehabilitation. The duration of the regular rehabilitation will be 60 min five times a week for four weeks. All interventions for the control group will be carried out by three experienced intermediate therapists separately.Study group (SG)In addition to receiving the same type of routine rehabilitation as the control patients, patients in the study group will also be required to undergo DBM and ADIM sessions. Each rehabilitation session for patients in the trial group will be divided into 40 min of regular rehabilitation and 20 min of DBM combined with ADIM training. The study group will complete 5 training sessions per week for 4 weeks in the same setting. All interventions for the study group will be delivered separately by three experienced intermediate therapists.

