### Outcomes {12}

Participants will be assessed within 1 week of admission at baseline and the end of 4 weeks. The primary outcome is the 10 m maximum walking test (10MWT). Secondary outcome measures include the limits of stability test (LOS), Berg balance scale test (BBS), Functional Ambulation Categories test (FAC), Timed Up and Go test (TUG), trunk impairment scale test (TIS), ultrasound indicators of the diaphragm and transversus abdominis (UI), rhythmic weight shift test (RWS), walk across test (WA), Fugl-Meyer assessment of lower extremity (FMA-LE), and Barthel index of ADL test.

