### Recruitment {15}

Following the proposed timeline, patient recruitment for this study will commence on September 1, 2022, and will continue until 1 year later or until the desired sample size is achieved. As this is a single-center clinical trial with a clear patient source, we will collect patients who meet the recruitment requirements from the hospital medical record system based on inclusion and exclusion criteria. To facilitate effective communication with patients, a comprehensive plan and methodology will be developed, which includes obtaining informed consent and conducting a video presentation explaining the study’s objectives and procedures. In addition, we will explain to subjects the advantages and disadvantages of the treatment and the relevant safety measures to be taken during the trial. Based on the recruitment criteria, the study team will initially estimate the likelihood of inclusion for each subject and, after the subject has signed the informed consent form, will carry out the relevant tests to confirm whether the subject conforms to the inclusion/exclusion criteria.

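### The interim analysis of the primary endpoint waits for 6 months of follow-up although outcomes are listed at 4 weeks, so under roughly even accrual it comes when little of the trial is left to stop or modify

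*Protocol article*

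**What the plan says.** Four sections of the protocol article bear on this point.

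- Interim analyses {21b} sets the trigger: "When 50% of patients have been randomized and completed 6 months of follow-up, the primary endpoint will undergo an interim analysis by a statistician". After review by the data monitoring committee, "the trial may be stopped or undergo appropriate modifications".
- Outcomes {12} sets the assessment times: "Participants will be assessed within 1 week of admission at baseline and the end of 4 weeks". It names the 10 m maximum walking test as primary and mentions no later time. The Abstract (Methods) likewise describes measurement after 4 weeks of intervention.
- Trial design {8} adds to the initial assessment "a final assessment post-trial, and a follow-up evaluation six months later". It does not say which outcomes are read at that evaluation.
- Recruitment {15} says that recruitment "will commence on September 1, 2022, and will continue until 1 year later or until the desired sample size is achieved".

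Sample size {14} gives the total of 42, so half is 21 patients.

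**The concern.** An interim analysis is useful only if its result arrives while there is still something to decide. Here the trigger is a follow-up milestone about six months later than the only post-baseline time at which the outcomes section reads the primary measure. Either the look waits for data that it does not need, or the interim section implies a 6-month primary reading that the outcomes section does not list. Both readings call for a correction, and neither depends on an accrual assumption.

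The practical consequence does depend on accrual. With a recruitment window of one year, a trigger that needs half the patients plus six months or more is likely to fall at about the end of enrolment. The primary comparison would then be made on 21 patients when the 4-week data of all 42 are complete or nearly so, and the committee would be asked about stopping or changing a trial that has almost run its course.

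**Working it through.** **Inputs**
- Total 42 (Sample size {14}); half is 21.
- Treatment "five times a week for four weeks" (Intervention description {11a}): 28 days / 30.44 days per month = 0.92 month.
- Recruitment window of 12 months from 1 September 2022 (Recruitment {15}).
- Accrual pattern: not given. Even accrual is assumed first, then varied.

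**The plan's own figure.** A two-sample t-test with effect size 1.1327272, two-sided 5% and power 0.90 needs 18 per arm, that is 36, as stated. 36 × 1.15 = 41.4, rounded up to 42, which reproduces the total. (Dividing by 0.85 would give 42.35, that is 43; this has no bearing here.)

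**Two readings of the lag L from randomisation to 6 months of follow-up**
- Counted from randomisation: L = 6.0 months.
- Counted from the post-treatment assessment, as Trial design {8} describes it: L = 0.92 + 6 = 6.92 months.

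**Even accrual over 12 months.** The 21st patient is randomised at 12 × 21/42 = month 6.0.
- L = 6.0: look at month 12.0, the day enrolment closes. With a 4-week reading: 42 × (12.0 − 0.92)/12 = 38.8, so about 3 patients are still in treatment.
- L = 6.92: look at month 12.9, about the end of September 2023. All 42 are enrolled and all 42 have reached the 4-week reading.

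**Other even rates.** If accrual takes T months, the look falls at T/2 + L. It precedes the end of enrolment only if T/2 + L < T, that is T > 2L: more than 12 months for L = 6.0, or more than 13.8 months for L = 6.92.

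| Accrual time T (months) | Look, L = 6.0 | Left to enrol | Look, L = 6.92 | Left to enrol |
|---|---|---|---|---|
| 3 | 7.5 | 0 | 8.4 | 0 |
| 6 | 9.0 | 0 | 9.9 | 0 |
| 9 | 10.5 | 0 | 11.4 | 0 |
| 12 | 12.0 | 0 | 12.9 | 0 |
| 15 (overrun) | 13.5 | 4.2 | 14.4 | 1.6 |
| 18 (overrun) | 15.0 | 7.0 | 15.9 | 4.9 |

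For example, with T = 18 and L = 6.0, enrolled = 42 × 15/18 = 35, leaving 7 (17%).

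**Uneven accrual within 12 months.** The look falls inside the window only if the 21st patient enters before month 12 − 6.0 = 6.0, or before month 12 − 6.92 = 5.1. As a strongly front-loaded case, take N(t) = 42 × √(t/12), which reaches 21 at month 3.
- Look at month 9.0: 42 × √(9.0/12) = 36.4 enrolled, 5.6 left.
- Look at month 9.9: 42 × √(9.92/12) = 38.2 enrolled, 3.8 left.

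Back-loaded accrual moves the look later still.

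**What is still open at the look.** With even accrual over 12 months, the last 6-month evaluation falls at 12 + 0.92 + 6 = month 18.9, so some of these visits would be outstanding.

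**A 4-week trigger for comparison.** With even accrual over 12 months, the 21st patient reaches the 4-week assessment at 6.0 + 0.92 = month 6.9, about the end of March 2023. Enrolled: 42 × 6.92/12 = 24.2, so about 24. Left to enrol: about 18, that is 18/42 = 43%.

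**The case against.** A reader might infer that the look is bound to fall after enrolment has ended and that it can neither stop nor modify the trial. The documents do not support so absolute a statement. They give no accrual rate. Counted from randomisation, the look lands on the closing day, not after it. The wording of Recruitment {15} does not clearly exclude an overrun, and front-loading or an overrun leaves a few patients to enrol. The 6-month evaluation is part of the trial process, so outstanding visits could be curtailed or changed. Interim analyses {21b} also lists safety and feasibility grounds for termination that do not hang on this trigger. All of this stands and limits the claim. It does not restore the usefulness of the look, because at most about 7 of 42 remain to enrol in the scenarios tried.

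Second, no sentence labels 4 weeks as the primary time point. It is a strong inference from the Abstract and Outcomes {12}. The schedule in Fig. 2 is not available here and may show which outcomes are read at 6 months. If the sponsor means a 6-month primary reading at the interim, the wait follows naturally and the defect is the disagreement between sections. That too stands, and it is why reconciliation comes first in the fix.

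Third, a reader might infer that the look wastes type I error. The article states no boundary or spending rule for it, and an analysis plan not shown here may do so. The point about timing does not need this claim.

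**Conclusion.** The point holds in a limited form. The interim trigger does not fit the outcome times: it waits for 6 months of follow-up for an endpoint that the Abstract and Outcomes {12} read at 4 weeks. That mismatch is in the text and needs no assumption beyond taking 4 weeks as the primary time.

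The size of the consequence rests on assumed accrual. With even accrual over the planned year the look falls at month 12.0 to 12.9, with nobody left to enrol and at most about 3 patients still in treatment. Faster even accrual gives the same picture. Strong front-loading or an overrun to 18 months leaves about 4 to 7 of 42. The look can therefore do little to stop or modify enrolment, treatment or the 4-week endpoint, which is most of what the interim section says it is for. The final 4-week comparison is not damaged by the timing, so this is a correction that should be made rather than a threat to the main result.

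**What to change.** First reconcile Trial design {8}, Outcomes {12} and Interim analyses {21b}. State the primary time point (4 weeks, as the Abstract and Outcomes {12} imply) and say whether the 6-month evaluation is secondary and which outcomes it carries. If a 6-month primary reading is intended, the Abstract and Outcomes {12} must say so instead.

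Then, with a 4-week primary time point, choose one of two courses:
- Delete the interim efficacy analysis and keep the committee's safety review.
- Trigger the look when the 21st randomised patient reaches the 4-week assessment (about month 7 under even accrual, with about 24 of 42 enrolled). Pre-specify a stopping boundary that keeps the overall two-sided type I error at 5%. The boundary is needed because two unadjusted tests at 5%, on half and then all of the data, give about 8%.

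Deletion costs only wording. The earlier look costs a slightly stricter threshold at the final analysis. Either course needs a protocol amendment while the trial is recruiting (Trial status), with the expert evaluation that the section on protocol amendments {25} requires for changes of design.

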### Sample size {14}

The study was a randomized controlled trial, with the 10 m maximum walking speed of the study participants as the main outcome indicator observed. The study was found by sample estimation with the G*Power 3.1 software, which, combined with previous studies, resulted in an effect size of 1.1327272, a power value of 0.9, and a significance level of *a* = 0.05, giving a sample size of 36 cases. Considering that there may be a 15% attrition rate during the trial, the required sample size was obtained. The final sample size was calculated to be 42 cases.

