### Procedure for unblinding if needed {17b}

If the following events occur during the trial, blinding will be lifted.:If the safety monitoring committee or data monitoring committee identifies an evident safety concern based on trial data that necessitate modifications to the trial or control group, or discontinuation of the trial, appropriate action will be taken.Immediate intervention will be warranted if a participant enrolled in the trial reports an apparent adverse reaction or side effect to the drug being tested.The results of the primary endpoint indicator of the trial have been sufficiently demonstrated that continued blinding is not required.

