## Statistical methods

### Statistical methods for primary and secondary outcomes {20a}

Statistical analysis of research data will be performed by health statisticians and major researchers using SPSS 24.0. The statistical tests will all be two-sided. The level of statistical significance will be set at 5%. The measured data will be presented as mean ± standard deviation. Paired *t*-tests will be used for within-group controls before and after the trial. Comparisons between the two groups will be made using *t*-tests or rank sum tests.

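### The trial is sized for one look at two-sided 5% with 90% power, but an interim on the primary endpoint may stop it with no stated boundary, so those error rates are not assured

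*Protocol article*

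**What the plan says.** Sample size {14} takes "an effect size of 1.1327272", then "a power value of 0.9, and a significance level of" 0.05, and arrives at 36 cases, raised to 42 for 15% attrition. Statistical methods {20a} states "The statistical tests will all be two-sided" and "The level of statistical significance will be set at 5" percent. It gives no separate level for an interim or a final test.

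Interim analyses {21b} plans an analysis of the primary endpoint once half the patients have been randomized and have finished six months of follow-up. The results go to the DMC, and "Based on the assessment by the DMC, the trial may be stopped or undergo appropriate modifications". The same section lists grounds for terminating the trial. Beside safety and feasibility it names "or failure to demonstrate a predetermined hypothesis", and it gives the decision to the DMC or the trial management team.

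Procedure for unblinding {17b} lists, as one reason to lift blinding during the trial: "The results of the primary endpoint indicator of the trial have been sufficiently demonstrated that continued blinding is not required".

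**The concern.** Three stated elements do not fit together: a sample size for one look, one 5% level, and an interim on the primary endpoint that can end or change the trial. A 5% level and 90% power describe the whole procedure, including any early stop. If the interim can end the trial on efficacy results, in either direction, the procedure's error rates depend on a rule that the protocol does not give.

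At stake is the primary inference of a superiority trial with 42 patients. A claim made at an early success stop could carry more than 5% type I error and an exaggerated effect. A stop because the hypothesis was not yet demonstrated could end a trial of a treatment that works as well as planned. Because the termination decision is also open to the trial management team, interim efficacy results could reach those who run the trial.

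**Working it through.** **Inputs.** Standardized effect d = 1.1327272, power 0.9, alpha 0.05, 36 evaluable and 42 in total (Sample size {14}); two-sided tests at 5%, t-test or rank sum test (Statistical methods {20a}); 1:1 allocation (Trial design {8}); interim at 50% of patients (Interim analyses {21b}).

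**Reproducing the plan's figure.** For a two-sided two-sample t-test, the noncentrality is d × √(n/2) with n per arm.
- n = 17: 1.1327 × √8.5 = 3.302, power 0.893.
- n = 18: 1.1327 × √9 = 3.398, power 0.910.

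So N = 36, and 36 × 1.15 = 41.4, rounded up to 42. The stated size is a single look at the full 5%, with nothing set aside for an interim.

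**Interim power at the planned effect.**
- 9 per arm (half of 36): noncentrality 1.1327 × √4.5 = 2.403, critical t (16 df) = 2.120, power 0.617.
- 10 and 11 per arm (all 21 of the first half of 42 evaluable): noncentrality 1.1327 × √(110/21) = 2.592, critical t (19 df) = 2.093, power 0.691.

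**Rule A: stop for success at p<0.05, otherwise test at 5% at the end.** With correlation √0.5 between the two statistics, alpha = 1 − P(|Z1| < 1.96 and |Z2| < 1.96) = 0.083. Simulated t-tests with 9 then 18 per arm give 0.084. Power is 0.920.

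**Rule B: stop whenever the interim is not significant.**
- If a significant interim counts as success, power is the interim power: 0.617 (9 per arm) or 0.691 (10 and 11).
- If significance is also required at the end, power is 0.607 or 0.685.
- An effective treatment at the planned d is stopped with probability 1 − 0.617 = 38%, or 1 − 0.691 = 31%.
- Alpha is 5% in the first version and 1.6% in the second, so it is not inflated.

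**Rule C: success at p<0.05, futility at p>0.2, otherwise a final test at 5%.** Simulated with 9 then 18 per arm: alpha 0.069, power 0.83.

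**Mild futility only: stop at p>0.5, one final test at 5%.** Power 0.89 at 18 per arm, against 0.910 for one look; alpha 4.6%.

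**Size of an early estimate under rule A.** With 9 per arm, significance needs an observed difference of about 2.120 × √(2/9) = 1.00 SD, using the estimated SD. If the true effect were 0.5 SD (an assumption), trials significant at the interim would report 1.14 SD on average.

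**Timing (assuming uniform accrual over the planned year).** Patient 21 of 42 enters at month 12 × 21/42 = 6. Adding four weeks of treatment and six months of follow-up gives about month 13. The last patient enters at month 12 and reaches the four-week assessment at about month 13. Recruitment would be over, and nearly all four-week data would exist at the interim.

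**O'Brien-Fleming, two looks at 50% and 100%.** Nominal two-sided levels are 0.0052 and 0.0480, for an overall alpha of 0.050. Simulated power at 18 per arm is 0.908, against 0.910 for one look.

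**The case against.** Each rule above is supplied by the reader. Interim analyses {21b} gives no threshold in either direction, and the 5% level stands under the methods for primary and secondary outcomes, without mention of the interim. An analysis plan or DMC charter that is not shown may hold a boundary. For example, interim p<0.001 with a final test at 0.05 gives an overall alpha of 5.02%. This stands, and it is why the error rates can be called unassured but not broken.

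No efficacy stop is named. The listed termination grounds do not include early success. That reading rests on the general permission to stop and on the unblinding section, which concerns lifting blinding and mentions a tested drug in an exercise trial. The 8.3% and the exaggerated estimate are therefore conditional.

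The 61–69% power treats a hypothesis-based termination as compulsory whenever p>0.05, although the text leaves room for the DMC's judgement. A mild futility rule costs about two points of power. If all 42 patients complete, single-look power is 0.947, which gives some cushion.

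Under uniform accrual the interim comes too late to discard much four-week data. This softens the consequence, and it also removes most of the reason for an efficacy look.

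What remains does not depend on an unseen document. The protocol itself states a single-look sample size, one 5% level, and a termination ground tied to the hypothesis and open to the trial management team.

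**Conclusion.** The point holds in conditional form. The stated 5% and 90% belong to a single-look design, and the interim section allows actions under which one or both figures fail: alpha of about 8.3% with a success stop at p<0.05, power of about 61–69% with a stop on a non-significant interim, or about 6.9% and 83% under the mixed rule. These figures assume t-tests, the planned effect, and an interim at half the final sample size: 9 then 18 per arm, or 10 and 11 then 21 per arm for the upper end of the power range.

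A reader might infer that alpha and power both fail as the plan is written. The documents do not support that: the two losses come from different rules and occur together only under a mixed rule. Nor do they support saying that the interim is set at 5%, that an early success stop is planned, or that an effective treatment would be dropped more than a third of the time. That last figure is 38% in the worst case and 31% if all 21 interim patients are evaluable.

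This should be fixed before the interim is carried out. It does not by itself invalidate the design.

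**What to change.** Preferred: limit the interim to safety and data quality, delete the ground that refers to failure to demonstrate the hypothesis, align the unblinding section, and keep one primary test at two-sided 5%. The sample size then stands as calculated. The cost is the loss of an early efficacy stop, which would save few or no patients if recruitment runs to plan.

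If an efficacy look is kept:
- state O'Brien-Fleming limits, two-sided about 0.005 at the interim and 0.048 at the end, in place of the single 5% level for the primary endpoint;
- make any futility guidance non-binding and do not base it on p>0.05;
- keep interim efficacy results with the DMC and away from the trial management team.

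The cost is a slightly stricter final threshold. Power at 18 per arm goes from 0.910 to about 0.908, so no extra patients are needed. Either route is a change of wording. If a boundary already exists in another document, cite it in the interim section and qualify the 5% statement accordingly.
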